#### Tertiary outcomes

Differences in perceived stress according to Cohen’s Perceived Stress scale, quality of life according to the WHOQOL-BREF score, self-rated depressive symptoms according to BDI, self-rated manic symptoms according to ASRM, recovery according to the Recovery Assessment Scale, empowerment according to Rogers Empowerment Scale and medicine adherence according to MARS between the intervention group and the control group.

No changes in trial outcomes have been made after trial commencement.

### Statistical power and sample size calculation

The statistical power and sample size was calculated using http://stat.ubc.ca/~rollin/stats/ssize/n2.html.

The primary outcomes are a) differences in the level of depressive and manic symptoms based on HDRS-17 and YMRS, respectively and b) differences in the number of depressive and manic episodes defined as HDRS ≥14 and YMRS ≥14, respectively.The clinical relevant difference in the level of depressive and manic symptoms is defined as a minimum of three scores on HDRS-17 and YMRS, respectively, and the standard deviation (SD) is set to 7 with a mean score of 7 vs. 10 in the intervention group and the control group, respectively. The statistical power to detect a three score difference in the areas under the curves between the intervention group and the control group on HDRS-17 and YMRS, respectively, is 80% with α = 0.05 for a two-sample comparison of means including a minimum of 86 patients in each of the two sub-groups in the intervention group (smartphones capable of collecting automatically generated behavioural data or not) (n = 172) and 86 patients in the control group (n = 86). This results in an estimated total sample size of 258 patients.The clinical relevant difference in the number of depressive and manic episodes is defined as a minimum of 10% difference and the SD is set to 23% with a mean score of 40% vs. 50% in the intervention group and the control group, respectively. The statistical power to detect a 10% difference in the area under the curves between the intervention group and the control group on the number of depressive and manic episodes is 80% with α = 0.05 for a two-sample comparison of means including about the same number of patients in each of the two sub-groups in the intervention group (smartphones capable of collecting automatically generated behavioural data or not) (n = 172) and in the control group (n = 86).

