### Outcomes

#### Primary outcomes

Differences in clinically rated depressive and manic symptoms measured using HDRS-17 and YMRS, respectively, between the intervention group and the control group.Differences in depressive and manic symptoms measured using HDRS-17 and YMRS, respectively, between the intervention group and the control group in patients with presence of depressive and manic symptoms (defined as HDRS-17 > 0 or YMRS > 0) *at any given visit* with the researcher during the 9-month trial period.Differences in depressive and manic episodes defined as HDRS-17 ≥14 or YMRS ≥14 between the intervention group and the control group.

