### Statistical methods

Data from all randomized patients are collected until dropout or the end of the trial period. Analysis will be carried out with an intention-to-treat (ITT) approach. The primary outcomes are differences in depressive and manic symptoms using HDRS-17 and YMRS, respectively, during the 9-month trial period. Analysis will be done employing a linear mixed effects model with random intercept for each participant and a fixed effect of visit number. Differences in outcomes between the intervention group and the control group will be analyzed, firstly in an unadjusted model (except for potential differences in baseline values of the outcome variable) and then in models adjusted for age and sex as possible prognostic variables.

Furthermore, analysis will be done employing a linear mixed effects model with random intercept for each participant and a fixed effect of visit on differences in HDRS-17 and YMRS in patients with presence of depressive and manic symptoms (defined as HDRS-17 > 0 or YMRS > 0) at a given time point during the trial period between the intervention group and the control group. Additionally, analysis of the primary outcomes of differences in depressive and manic episodes defined as HDRS ≥14 and YMRS ≥14 during the trial period will be done employing survival analysis with reasons for censoring being date of death or date of drop out.

Potential interactions between randomization group (intervention group or control group) and visit number in the analyses will be investigated and reported accordingly. The statistical threshold for significance is p ≤ 0.05 (two-tailed). Data will be managed by [name] and entered using Epidata® (Epidata Association, Odense, Denmark). All analyses will be done using STATA version 12 (StataCorp LP, College Station, TX, USA).

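### The 80% power stated for the episode outcome rests on an unsourced SD of 23%; if 40% and 50% are per-patient 9-month risks, power is about 33% (about 26% per sub-group against control)

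*Protocol article*

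**What the plan says.** Three sections of the Protocol article bear on this.

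- **Primary outcomes** lists "Differences in depressive and manic episodes defined as HDRS-17 ≥14 or YMRS ≥14". This is a threshold on a rating-scale score.
- **Statistical power and sample size calculation** treats the same outcome as continuous, with a relevant difference "defined as a minimum of 10% difference and the SD is set to 23% with a mean score of 40% vs. 50" (per cent). Power is stated as "on the number of depressive and manic episodes is 80% with α = 0.05 for a two-sample comparison of means", with about 86 patients in each of the two intervention sub-groups (172 together) and 86 controls. No source is given for the 23%, and the section does not say what quantity the 40% and 50% measure.
- **Statistical methods** says that the analysis of episodes "will be done employing survival analysis with reasons for censoring being date of death or date of drop out", with two-sided significance at 0.05.

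The total of 258 is derived from the HDRS-17 and YMRS calculation in the same section. The episode calculation follows as a second justification for about the same numbers.

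**The concern.** A yes/no event has no free standard deviation: once the proportion is fixed, so is the SD. At 40% and 50% it is more than twice the 23% used. Required sample size grows with the square of the SD, so the gap is large. The sizing method (a difference in means) is also not the planned analysis (survival).

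Episodes are a declared primary outcome, and the Discussion ties wider use of the system partly to a lower episode rate. A reader told that this outcome has 80% power would take a null result as fair evidence against the stated relevant difference. If the true power is near one third, the trial would miss that difference about two times in three. The stake is interpretive; low power does not raise the type I error rate.

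**Working it through.** **Inputs from the article:** 40% vs 50%, SD 23%, two-sided α 0.05, 80% power, 172 intervention and 86 control patients, and ratings at baseline, 4 weeks, 3, 6 and 9 months. No dropout is allowed for in the power section, so none is applied here.

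**1. The article's own figure.** n per group = 2 × (1.960 + 0.842)² × 23² / 10² = 83.04, so 84. Power at 86 vs 86 is 81.4%. The stated 80% is therefore reproduced, as a pairwise figure with about 86 per group. With the same SD, 172 vs 86 would give 90.9%.

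**2. SD of a once-per-patient event.** √(0.40 × 0.60) = 49.0% and √(0.50 × 0.50) = 50.0%.

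**3. Two proportions, 172 vs 86.** The pooled proportion is (0.40 × 172 + 0.50 × 86)/258 = 111.8/258 = 0.433. The null standard error is √(0.433 × 0.567 × (1/172 + 1/86)) = 0.0654, and the alternative standard error is √(0.24/172 + 0.25/86) = 0.0656. Then (0.10 − 1.960 × 0.0654)/0.0656 = −0.431, so power is 33.3%. The same steps for 86 vs 86 (standard errors 0.0759 and 0.0755) give −0.645 and power 25.9%.

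**4. Log-rank, the planned type of analysis.** Assume proportional hazards and that 40% and 50% are 9-month first-event risks. HR = ln 0.6/ln 0.5 = 0.737, and expected events are 111.8. Then |ln HR| × √(111.8 × 1/3 × 2/3) = 0.305 × 4.98 = 1.52, and 1.52 − 1.96 = −0.44, so power is 33.0%. For 80% power, (1.960 + 0.842)² / (2/9 × 0.305²) gives about 380 events, more than the 258 patients planned.

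**5. Share-of-visits reading (an assumption; the article does not define it).** With m visits and within-patient correlation ρ, SD = √(0.2475 × (1 + (m − 1)ρ)/m), where 0.2475 = 0.45 × 0.55.

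| Visits | ρ | SD | Power 172 vs 86 | Power 86 vs 86 |
|---|---|---|---|---|
| 4 | 0 | 24.9% | 86% | 75% |
| 4 | 0.3 | 34.3% | 60% | 48% |
| 4 | 0.5 | 39.3% | 49% | 38% |
| 4 | 0.7 | 43.8% | 41% | 32% |
| 5 | 0 | 22.2% | 93% | 84% |
| 5 | 0.1 | 26.3% | 82% | 70% |

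Four visits are the post-randomization ones; five include baseline. The correlations are assumed, since the article gives none. An SD of 23% corresponds to ρ of about −0.05 with four visits and about +0.02 with five.

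**6. Detectable difference at 80% power, 172 vs 86.** For two proportions at 50% vs 32%, the standard errors are 0.0641 and 0.0646, and (0.18 − 1.960 × 0.0641)/0.0646 = 0.84, so power is 80%. That pair corresponds to HR = ln 0.68/ln 0.5 = 0.556. For the log-rank test the event count falls as the effect grows and must be recomputed. At HR 0.55 the intervention risk is 1 − 0.5^0.55 = 31.7% and events are 172 × 0.317 + 43 = 97.5. Then 0.598 × √(97.5 × 2/9) = 2.78, which gives power of about 79.5%. The hazard ratio detectable with 80% power is therefore about 0.55.

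**The case against.** The best defence is that the power section does not describe a yes/no event at all. It refers to a mean score, to areas under the curves and to the number of episodes, which suggests a per-patient summary over visits. Such a summary has a smaller SD than a single event, and with all five ratings and independent visits the SD is 22.2%, just below 23%.

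Part of this stands. A reader might infer that an SD of 23% is impossible for this outcome; the article does not support that, because the 40% and 50% are never defined. Nor does it support 33% as the power of the design without conditions: that figure needs 40% and 50% to be 9-month first-event risks. It also applies to 172 vs 86, whereas the article's 80% is reproduced pairwise at 86 vs 86, where the matching figure is 26%.

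The defence does not rescue the stated power. The share of visits in episode is neither listed as an outcome nor analysed. Baseline precedes randomization and cannot carry a treatment effect, and with the four later visits, power at 86 vs 86 is 75% even at zero correlation. The window in which 172 vs 86 keeps 80% power is narrow: ρ up to about 0.06 with four visits, or 0.12 with five. The plan fits a random intercept per participant to the underlying scores, which anticipates positive within-patient correlation.

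It is also fair to say that the 258 comes from the symptom-score calculation. An error here does not undo that sample size.

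**Conclusion.** The concern holds in a conditional form. The 80% power for episodes is not supported as written: it depends on an unsourced SD and on a comparison of means that matches neither the threshold definition nor the planned survival analysis. The fault lies in the input, not in the arithmetic.

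If the percentages are once-per-patient 9-month risks, power is about 33% for the whole intervention group against control (two proportions, or log-rank under proportional hazards) and about 26% for each sub-group against control. If they are shares of four visits with an assumed correlation of 0.3–0.7, power is about 60–41% and 48–32% respectively. All figures are before dropout, which would lower them.

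A reader might go further and conclude that the trial must be enlarged or that episodes must cease to be a primary outcome. Neither follows. Low power does not by itself disqualify a primary outcome, and reclassifying one while recruitment is under way would be a substantive amendment. Reaching 80% power for 40% vs 50% at 2:1 would take about 290 + 580 = 870 patients, against roughly 400 potential participants reported under Participants and settings.

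**What to change.** In the power section:

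- Delete the calculation based on an SD of 23%.
- State what the 40% and 50% are and replace the calculation with one that matches the survival analysis.
- If they are 9-month risks, say that 258 patients give about 33% power for 40% vs 50%, and about 26% for each sub-group against control, before dropout.
- Add that the difference detectable with 80% power at 172 vs 86 is about 50% vs 32%, a hazard ratio of about 0.55.

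Report the episode result as an estimate with a confidence interval, so that a non-significant result is not read as no effect.

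The sample size and the outcome's primary status stay as they are. The change is to wording and costs only a less favourable power figure.

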### Blinding

Owing to the type of intervention in the MONARCA II trial, the patient, the patients’ health care provider and the MONARCA II study nurse are aware of the allocated randomization group. The researchers responsible for outcome assessments, data entry, data analysis, interpretation of analysis and writing of papers are kept blinded to allocation at all times during the trial period, data analysis and interpretation of analysis. The trial is therefore single-blinded. The MONARCA II study nurse does not collect any outcome measures. All patients are thoroughly and at each visit with the researcher instructed not to mention anything about randomization allocation. The risk of unblinding due to simply seeing the patients’ smartphone is minimized since all patients use a smartphone during the trial period.

### Statistical methods

Data from all randomized patients are collected until dropout or the end of the trial period. Analysis will be carried out with an intention-to-treat (ITT) approach. The primary outcomes are differences in depressive and manic symptoms using HDRS-17 and YMRS, respectively, during the 9-month trial period. Analysis will be done employing a linear mixed effects model with random intercept for each participant and a fixed effect of visit number. Differences in outcomes between the intervention group and the control group will be analyzed, firstly in an unadjusted model (except for potential differences in baseline values of the outcome variable) and then in models adjusted for age and sex as possible prognostic variables.

Furthermore, analysis will be done employing a linear mixed effects model with random intercept for each participant and a fixed effect of visit on differences in HDRS-17 and YMRS in patients with presence of depressive and manic symptoms (defined as HDRS-17 > 0 or YMRS > 0) at a given time point during the trial period between the intervention group and the control group. Additionally, analysis of the primary outcomes of differences in depressive and manic episodes defined as HDRS ≥14 and YMRS ≥14 during the trial period will be done employing survival analysis with reasons for censoring being date of death or date of drop out.

Potential interactions between randomization group (intervention group or control group) and visit number in the analyses will be investigated and reported accordingly. The statistical threshold for significance is p ≤ 0.05 (two-tailed). Data will be managed by [name] and entered using Epidata® (Epidata Association, Odense, Denmark). All analyses will be done using STATA version 12 (StataCorp LP, College Station, TX, USA).

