### Assessments

All assessments are carried out by one researcher ([name]) who is not involved in the treatment of the patients. The bipolar disorder diagnoses according to ICD-10 are confirmed by a SCAN interview before inclusion of the patients. The patients are, regardless of randomization group, enrolled for a 9-month trial period and invited for outcome assessments by a blinded researcher ([name]) at baseline, after 4 weeks, after 3 months, after 6 months and after 9 months (Table 1).

At each visit with the researcher the assessments include the following: The severity of depressive and manic symptoms is measured using HDRS-17 item and YMRS, respectively, and psychosocial functioning is measured using the Functioning Assessment Short Test (FAST) [38]. The following questionnaires are fulfilled when visiting the researcher: perceived stress according to Cohen’s Perceived Stress scale [39], quality of life according to WHO Quality of Life-BREF (WHOQoL-BREF) [40], self-rated depressive symptoms according to Becks Depressive Inventory (BDI) [41–43], self-rated manic symptoms according to Altman Self Rating scale for Mania (ASRM) [44], recovery according to Recovery Assessment Scale (RAS) [45], medicine adherence according to Medicine Adherence Rating Scale (MARS) [46] and empowerment according to Rogers Empowerment Scale (RES) [47].

Furthermore, the patients are asked to show up fasting between 8–10 A.M. at baseline, after 4 weeks, 3 months, 6 months and 9 months when visiting the researcher and the following biological samples are collected: 1) Blood samples obtained by venipuncture, 90 ml in total and 2) a freshly voided morning spot urine sample (around 20 ml). The biological samples will be analyzed at the end of the trial for candidate biological markers that are potentially related to alterations in illness activity and affective state in bipolar disorder.

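### If scores correlate less the further apart the visits lie, the random-intercept model misstates the standard errors of the group-by-visit terms, while the averaged group effect stays sound

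*Protocol article*

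**What the plan says.** The Statistical methods section of the protocol article specifies, for HDRS-17 and YMRS, a "linear mixed effects model with random intercept for each participant and a fixed effect of visit number". It uses the same structure again for visits with symptoms present, this time calling the fixed effect simply visit. It does not say whether visit enters as a number or as categories. It mentions no random slope, residual correlation structure or robust standard error. The first analysis is described as "firstly in an unadjusted model (except for potential differences in baseline values of the outcome variable"), which reads most naturally as baseline entered as a covariate.

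The section then says: "Potential interactions between randomization group (intervention group or control group) and visit number in the analyses will be investigated and reported accordingly". The significance threshold for all analyses is 0.05, two-tailed. Assessments take place "at baseline, after 4 weeks, after 3 months, after 6 months and after 9 months" (Assessments section), so the follow-up visits are unequally spaced.

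**The concern.** A random intercept with independent residuals gives every visit the same variance and every pair of visits the same correlation. Scores taken 4 weeks and 3 months after inclusion are treated as no more alike than scores taken at 4 weeks and 9 months. The protocol describes bipolar disorder in terms of prodromes, deterioration and episodes. In an episodic illness it is reasonable to expect nearby scores to agree more closely than distant ones.

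If so, the model's single within-patient variance is too small for comparisons across long gaps and too large for comparisons across short ones. The interaction is where this shows, because it asks whether the group difference changes over time. At stake is a pattern of growing or fading benefit or harm reported as real more often than the stated 5% when none exists. The background of this trial makes such a pattern interesting: the predecessor trial found no overall difference, but its sub-analyses pointed to more sustained depressive symptoms with self-monitoring.

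**Working it through.** **The plan's own figure.** With a difference of 3, SD 7, two-sided 5% and 80% power: n = 2 × (1.960 + 0.842)² × 7² / 3² = 85.5, so 86 per group and 3 × 86 = 258 in total. This reproduces the stated sample size (power 0.802 at 86 per group). The plan states no achieved error rate for the interaction, only the 5% threshold.

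**Inputs.** Follow-up visits at 0.92, 3, 6 and 9 months (Assessments). 172 versus 86 patients and SD 7 (sample size section). The correlation between visits is *assumed*: S = r + (1 − r)·exp(−d/τ), where d is the gap in months.

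**Formula.** For a contrast c across visits (coefficients summing to zero), the true variance is proportional to c′Sc. The random-intercept model uses w·c′c, with w = 1 − mean off-diagonal correlation. With V = c′Sc / (w·c′c), actual type I error is 2Φ(−1.96/√V). A common baseline coefficient cancels out of such contrasts, and r cancels out of V, so only τ matters.

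**Worked case, r = 0, τ = 6.** The six correlations are 0.707, 0.429, 0.260, 0.607, 0.368 and 0.607. Their mean is 0.496, so w = 0.504.
- Linear slope, c = (−3, −1, 1, 3), c′c = 20: c′Sc = 17.2, V = 17.2 / (0.504 × 20) = 1.71, √V = 1.31, type I error 13.4%.
- 9 months minus 4 weeks: V = (1 − 0.260)/0.504 = 1.47, type I error 10.6%.
- 3 months minus 4 weeks: V = (1 − 0.707)/0.504 = 0.58, type I error 1.0%.
- 6 minus 3 months: V = (1 − 0.607)/0.504 = 0.78, type I error 2.7%. The same holds for 9 minus 6 months.

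**Range over τ, no visit-level noise.**

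| τ (months) | V, linear slope | Linear slope | 9 months − 4 weeks | 3 months − 4 weeks | 6 − 3 and 9 − 6 months |
|---|---|---|---|---|---|
| 3 | 1.46 | 10.5% | 8.3% | 1.8% | 3.5% |
| 6 | 1.71 | 13.4% | 10.6% | 1.0% | 2.7% |
| 12 | 1.87 | 15.2% | 12.2% | 0.7% | 2.1% |

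**With visit-level noise.** The form above lets correlation approach 1 as the gap shrinks, which leaves no room for rating error. Using off-diagonal correlation a + b·exp(−d/τ), with a = 0.2-0.3, b = 0.2-0.5 and τ = 3-12 (also assumed), the linear slope has type I error 5.9-9.7%, 9 months minus 4 weeks 5.6-8.1%, and adjacent-visit contrasts 2.5-4.7%. Fixing noise at 20-40% of the variance instead, with r = 0 or 0.2, puts the slope at 7.5-10.7%.

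**Simulation of the joint and averaged tests** (172 versus 86, complete data, 6000 runs per scenario, visit as categories).
- Joint interaction test under constant correlation: 4.7-5.6%, which is noise around 5%.
- Joint interaction test under decaying correlation: 5.1-7.1% with baseline as a covariate, and 5.7-8.6% with baseline as a fifth outcome visit.
- Full REML fits (1500 runs, no dropout or 20% random dropout) under decay: 5.2-7.3%.
- Group effect averaged over visits: 4.5-5.9% in all scenarios.

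**The case against.** The strongest reply is that the plan's main analysis is sound. The primary outcomes are group differences over the 9-month period, and that averaged effect keeps its nominal error rate in every scenario tried. This stands, and it limits the point to a supporting analysis.

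Second, the excess depends on a decaying correlation that the documents do not report. Under constant correlation the interaction test is at 5%. This also stands. Nor do the documents support the tempting inference that the tests simply run above 5%.

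Third, the largest figures need visit to enter as a linear number and no visit-level noise. The protocol does not settle the first, and the second is unlikely for rating scales. With visit as categories the joint test is off by about two points at most when baseline is a covariate. This stands as a limit on size.

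A reader might also infer that all comparisons between visits are too liberal, or that a significant interaction would displace the overall result. Neither is supported. Adjacent-visit contrasts err in the conservative direction, the plan names no specific visit contrasts, and it contains no rule that lets the interaction decide what is reported.

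Finally, residual covariance may be settled in an analysis plan that is not shown. That is possible. But the article does not leave the structure open: it names a random intercept for each participant and commits to the interaction from these analyses, so the point concerns a stated choice.

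**Conclusion.** The point holds in conditional form. Given independent residuals, model-based standard errors and correlation that falls with time, the group-by-visit standard errors are too small for trends and distant visits and too large for adjacent ones. The size depends on how the interaction is tested:

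- Linear slope on visit number: type I error about 6-15% overall, and about 6-10% with visit-level noise (just under 11% at most in the settings tried).
- Joint test with visit as categories and baseline as a covariate: about 5-7%.
- Adjacent-visit contrasts: below 5%.
- Averaged group effect: near 5%.

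Every figure above 5% rests on assumed correlations. The validity of the averaged primary comparison is not affected. This is a cheap improvement to a supporting analysis.

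**What to change.** State that visit enters as categories, with an unstructured residual covariance over the four follow-up visits in place of the random intercept. Take both the group effect averaged over visits and the group-by-visit interaction from that one model. The alternative, useful if the first does not converge, is to keep the random intercept and use standard errors robust to clustering by patient.

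The cost is one sentence in the plan and a change to the model command. The unstructured covariance has 4 × 5 / 2 = 10 parameters instead of 2, a minor burden with about 258 patients. Recruitment was ongoing when the article was written, so the choice can be fixed before analysis.

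### The plan does not commit the survival analysis of primary episodes to the continuous baseline HDRS-17 or YMRS score

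*Protocol article*

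**What the plan says.** The Primary outcomes section of the protocol article lists "Differences in depressive and manic episodes defined as HDRS-17 ≥14 or YMRS ≥14 between the intervention group and the control group". Under Statistical methods, the symptom scores get a linear mixed model. The next sentence says that group differences in outcomes are analysed "firstly in an unadjusted model (except for potential differences in baseline values of the outcome variable"), and then with age and sex added. A second mixed model follows, for visits with symptoms present. Only after that are episodes given a different method: their analysis "during the trial period will be done employing survival analysis with reasons for censoring being date of death or date of drop out". That sentence gives the censoring reasons and nothing about covariates.

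Two other sections bear on the point. Randomization says that the trial's analyses will be adjusted for age and sex, without limiting this to any outcome. Assessments says that at each visit, baseline included, "The severity of depressive and manic symptoms is measured using HDRS-17 item and YMRS, respectively". Table 1 also shows the rating scales at baseline.

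**The concern.** An episode is defined by the HDRS-17 or YMRS score reaching 14 at a visit, so the patient's own starting score on that scale is the natural predictor of the event. Entry sets no symptom limit and randomisation is unstratified. Starting scores can therefore vary widely, and only chance balances them between arms.

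The adjustment rule was evidently written with a continuous outcome in mind. For the mixed model, the baseline value of the outcome variable is plainly the baseline score. For a thresholded outcome there are three possible readings: no baseline term, a yes/no term at 14, or the continuous score. Each gives a different model and a different power, and the article does not choose among them. Episodes are a primary outcome, and the article's closing argument for wider use of the system rests partly on them.

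**Working it through.** **1. The plan's own figure.** Inputs from the sample size section: for symptoms, "the standard deviation (SD) is set to 7 with a mean score of 7 vs. 10 in the intervention group and the control group, respectively"; for episodes, "the SD is set to 23% with a mean score of 40% vs. 50% in the intervention group and the control group, respectively"; power 80%. The threshold in Statistical methods: "The statistical threshold for significance is p ≤ 0.05 (two-tailed").

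n per group = 2(1.960 + 0.842)² × (SD/difference)² = 15.70 × (SD/difference)²

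- Symptoms: 15.70 × (7/3)² = 85.5, so 86.
- Episodes: 15.70 × (23/10)² = 83.0, so 84 after rounding up.

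Both agree with the stated 86 per group. With 86 vs 86, power is 80.2% and 81.4%.

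**2. Moving to the planned analysis.** The power statement treats the 40% and 50% as means, whereas the analysis is time to event. To study a covariate in a survival model I read them as the proportions ever reaching 14 at a follow-up visit. This is an assumption.

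- Hazard ratio under proportional hazards: ln 0.6 / ln 0.5 = 0.737.
- Events without dropout: 172 × 0.40 + 86 × 0.50 = 111.8.
- Schoenfeld: √(111.8 × 1/3 × 2/3) × |ln 0.737| = 4.984 × 0.305 = 1.52. Power = Φ(1.52 − 1.96) = 33%.

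**3. Effect of the continuous baseline score.** Simulation: normal scores at baseline and the four follow-up visits, with equal correlation ρ between any two visits. The threshold was set so that 50% of controls ever cross it, and a constant shift gives 40% in the intervention group. First crossing was analysed by discrete-time proportional hazards (complementary log-log with visit effects), 172 vs 86, two-sided 0.05, 1,500 runs per case. The article gives no ρ, so a range is shown.

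| ρ | No baseline term | Continuous score | Gain, points |
|---|---|---|---|
| 0.3 | 35.5% | 39.5% | 4.0 |
| 0.5 | 35.7% | 45.2% | 9.5 |
| 0.6 | 35.2% | 47.9% | 12.7 |
| 0.7 | 37.5% | 55.9% | 18.4 |

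With no true effect and ρ = 0.5, the rejection rates were 5.6% without and 5.5% with the score. The simulation error is √(0.05 × 0.95/1500) = 0.6 points, so both are compatible with 5%.

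**4. Against yes/no baseline status.** This is the comparator if the adjustment sentence does carry over. With 1,000 runs per case, power at ρ = 0.5 was 41% with yes/no status and 45% with the continuous score, a gain of 4 points. The gain was about 2 points at ρ = 0.3 and 8 at 0.7. A smaller run (500 per case) gave 39% vs 40%, 42% vs 43% and 47% vs 54% at ρ = 0.3, 0.5 and 0.7. Each of those figures has a simulation error of about √(0.4 × 0.6/500) = 2.2 points.

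**5. If patients already at 14 leave the risk set.** Without vs with the continuous score: 35.5% vs 37.8% at ρ = 0.3, 34.6% vs 38.6% at 0.5, and 35.6% vs 43.3% at 0.7. The gains are 2.3, 4.0 and 7.7 points. Allowing for simulation error, about 1 to 8 is a fair range.

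**6. Where the gain comes from.** In a Cox model, adjustment does not shrink the standard error as it does in a linear model. The gain comes from a conditional hazard ratio further from 1. In a separate Cox simulation (3,000 runs per case) with the same event proportions, a covariate with log hazard ratio 1.0 per SD moved the hazard ratio from 0.737 to 0.673 and power from 36.5% to 54.8%. With 0.3 per SD, power moved only from 34.1% to 35.9%, and with no prognostic effect it did not change beyond simulation error.

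**The case against.** The strongest reply is that the adjustment sentence refers to outcomes in general and so already covers episodes. The Randomization section, too, applies age and sex to the analyses as a whole. A reader might therefore infer too much in saying that the episode analysis is left without any covariate. The text does not support that: age and sex are promised, and a baseline term may be. What survives is narrower. On no reading is the continuous score clearly promised, because the outcome variable here is a dichotomy.

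A second reply is that this is a journal article, and that the model type, the time origin and the handling of ties belong in an analysis plan that is not shown. That is right for those details, and none of them is raised here. The article does, however, state an adjustment rule for its outcomes, and that rule is ambiguous for this one.

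Three stronger readings also fail:

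- A fixed loss of about 9 points. That figure needs an assumed correlation of 0.5 and the comparison with no baseline term at all. Against yes/no status the gain at 0.5 is about 4 points or less.
- Bias. The hazard ratio without the score is a different, valid quantity, the type I error is held, and chance imbalance after randomisation is not bias.
- A free gain. Adjustment makes the hazard ratio conditional on baseline severity.

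**Conclusion.** The point holds as an efficiency and clarity issue. The plan does not fix whether or how baseline severity enters the survival model for a primary outcome, and it does not commit to the most informative form of a measurement that it already takes.

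Assuming a between-visit correlation of 0.3 to 0.7, the continuous score is worth about 4 to 18 points of power over no baseline term, about 2 to 8 over yes/no status, and about 1 to 8 if patients at 14 or above at baseline are removed from the risk set. These ranges rest on reading 40% vs 50% as ever reaching 14, on 172 vs 86 patients without dropout, and on one normally distributed score with equal correlations. A combined HDRS-17/YMRS endpoint, or strongly skewed scores, would change them.

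The change does not resolve the low power of the episode comparison. Even with the score, power is about 40% to 56% on this reading. That shortfall comes from powering the outcome as a comparison of means with SD 23%, which is a separate matter.

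**What to change.** Add one sentence under Statistical methods. The main survival model for depressive episodes includes the continuous baseline HDRS-17 score and that for manic episodes the continuous baseline YMRS score; a combined endpoint includes both. Age and sex enter in the second model, as already planned. Keep the estimate without the baseline score as a supporting analysis.

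No new data are needed, and recruitment is described as ongoing, so this can be fixed before analysis. The cost is in interpretation: the main hazard ratio is conditional on baseline severity and should be labelled so when reported.
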